**Fig. 3 Fig3:**
[figure not shown]
Timeline for data collection in months and participant contacts by group

### Intervention

#### Autonomy support intervention group

Teachers in schools allocated to the intervention condition will receive the twelve-hour interactive autonomy support teacher-training program developed specifically for this study. The program aims to familiarize PE teachers with techniques and strategies aimed at promoting students autonomous motivation toward out-of-school activities. The program focuses on six sets of autonomy-supportive strategies and techniques: Taking students’ perspective, using non-controlling and informational language, providing a rationale, displaying patience, providing choices, and accepting negative emotions and feelings. The techniques are adapted from the strategies identified in previous autonomy support training programs [34–37]. The training will be delivered by two trained teacher trainers with extensive experience of PE and teacher education. The trainers will undergo a familiarization session with the core research team in which they will be introduced to the training material (manual, power point presentations, supportive material) and provided with instruction on how to deliver the program prior to implementation of the training. A summary of session content and related delivery techniques are presented in Table 1.

**Table 1 Tab1:** Description of teacher training program: Content and matched behaviour change techniques for each session

Session topic	Content	Behaviour change techniques^a^
1. Introduction and added value of the training to teaching practice	Introduction and warm up activities Information on the added value of the training and expectations Explore current supportive style and reflection Why autonomy support matters Introduction to self-determination theory	Social support (unspecified) Social support (practical) Discrepancy between current behaviour and goal Shaping knowledge Information about social and environmental consequences Imaginary reward
2. Autonomy supportive techniques: Description and benefits for students and teachers	Basics of the autonomy supportive teaching techniques: Definitions and implementation examples Using autonomy supportive techniques: Benefits for students and teachers based on previous research results	Demonstration of the behaviour Shaping knowledge Information about social and environmental consequences Behavioural practice/rehearsal
3. Use of autonomy supportive techniques to provide instructions	How, when, and why to use autonomy supportive techniques when giving instructions (organizational, technical and tactical) Taking students’ perspective Using non-controlling and informational language Providing rationale Providing choices Displaying patience	Information about social and environmental consequences Instruction on how to perform a behaviour Behaviour substitution Habit reversal Framing/ reframing Self-monitoring of behaviour Behavioural experiments Behavioural practice/rehearsal Graded tasks
4. Use of autonomy supportive techniques to provide feedback, encouragement, and praise	How, when, and why to use autonomy supportive techniques when providing feedback, encouragement, and praise Using non-controlling and informational language Taking students’ perspective Displaying patience	Generalization of a target behaviour Behaviour substitution Habit reversal Framing/ reframing Information about social and environmental consequences Instruction on how to perform a behaviour Self-monitoring of behaviour Behavioural experiments Behavioural practice/rehearsal Graded tasks
5. Use of autonomy supportive techniques to deal with discipline issues and off-task behaviours	How, when, and why to use autonomy supportive techniques when dealing with discipline issues and off task behaviours Taking students perspective Accepting negative affect Providing rationale Using non-controlling and informational language Displaying patience Providing choices	
6. Building personalized action plans	Plan changes in own teaching practice: Specific goals and plans for change when giving instructions, provide feedback, and respond to students with low motivation Identify barriers and problem solving for using the autonomy supportive techniques in every day teaching practice Development of their individualized infographic poster	Generalization of a target behaviour Goal setting Action planning (and implementation intention) Instruction on how to perform a behaviour Prompts/cues Adding objects to the environment Pros and cons Social support unspecified

^a^ From behaviour change technique taxonomy (Version 1) [66]

The teacher training was developed in three stages. In the first stage, we identified the most effective autonomy supportive techniques and means to deliver them to PE teachers based on current evidence. We therefore reviewed the existing literature on autonomy support techniques and training programs. Previous successful applications of autonomy support interventions in general classroom [38] and PE settings [39], as well as feasibility [36] and conceptual articles on autonomy support [34, 40] were identified. In addition, we acquired teacher training material from existing autonomy support training programs used in previous interventions [35, 37]. Next, we developed a list of training activities and delivery techniques considered effective and relevant to the proposed intervention. We also conducted a mapping exercise guided by a recent study outlining self-determination theory techniques and constructs [23] to ensure that the training activities and delivery techniques precisely matched the theory-based motivational determinants (e.g., autonomous motivation, psychological need satisfaction) targeted in the intervention.

The second stage involved the development of a detailed draft of the teacher training program. For each session, we developed a detailed description of the program content including aims, learning outcomes, main instructional points, examples, and interactive activities. Accompanying supportive materials (worksheets, printed examples, video demonstrations, presentation slides, and session’s summaries) were produced for illustration of the program content. The content and materials were reviewed and revised by the core research team.

The third and final stage involved review and revision of the entire program and materials by external stakeholders and teacher educators. Reviewers were experienced PE teachers and teacher-training experts, and researchers with expertise in the theoretical approaches on which the program was based, the delivery techniques used, and behavioural interventions conducted in school settings*.* The stakeholders reviewed each session content in detail in an interactive workshop with the research team. They also provided written feedback on the materials separately. Stakeholders identified issues relating to the clarity of the aims and descriptions, relevance of the examples, and overlap and redundancy in the materials. The program content and materials were further revised by the research team resulting in a final autonomy support training program with supporting materials.^1^

#### Wait-list control group

Participating teachers allocated to the waitlist control group will receive an alternative training program comprising 4-h of education on how to apply a monitoring system for physical functional capacity for children with special needs [33]. The control intervention is delivered in a one-day workshop by two educators experienced in PE teacher training.

### Outcome measures

All self-report outcome measures were translated from English into Finnish using a back-translation process by two bilingual researcher [41].

#### Primary outcome variable

The primary outcome measure is students’ post -intervention participation in out-of-school physical activity at the pre-trial, post-trial, one-, three and 6 month follow-up data collection occasions. Physical activity participation will be measured using the short form of the International Physical Activity Questionnaire, IPAQ [42], which will be modified to make explicit reference to out-of-school physical activity. The IPAQ comprises four items recording the frequency (number of days) and duration (hours) of participation in moderate and vigorous physical activity, walking, and sitting over the past 7 days. The physical activity score for moderate and vigorous physical activity and walking is calculated based on norms and expressed in MET-minutes per week. A score for total physical activity in out-of-school contexts is provided by the sum of the duration and frequency of vigorous, moderate and light physical activity scores. The IPAQ has acceptable concurrent validity and reliability indices [43].

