## Abstract

**Background:**

Given the documented decline in levels of physical activity in early adolescence, promoting physical activity in young people is a priority for health promotion. School physical education (PE) is an important existing network in which participation in physical activity beyond school can be promoted to the captive young people. The objective of current article is to present the protocol for a PE teacher-delivered theory-based trial to promote secondary school students’ participation in physical activity out-of-school contexts. The intervention will be guided by the trans-contextual model explaining the processes by which PE teachers’ support for autonomous motivation in the classroom promotes students’ motivation to engage in out-of-school physical activity. We hypothesize that school students receiving the teacher-delivered intervention to promote autonomous motivation toward physical activity will exhibit greater participation in physical activities outside of school, relative to students receiving a control intervention.

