### Sample size

A statistical power analysis was conducted to estimate the required sample size for student data based on a path analysis according to published recommendations [56]. The analysis was based on a model in which the primary outcome variable of student’s participation at each post-intervention follow-up occasion was regressed on the intervention condition (dummy coded as 1 = received intervention, 0 = received control) and constructs from the trans-contextual model (perceived autonomy support, autonomous motivation in PE and out-of-school, attitudes, subjective norms, perceived behavioural control, and intentions) as simultaneous predictors. Statistical power (beta) was set at 0.90 and statistical significance level (alpha) was set at 0.05, and confidence intervals of 0.068 and 0.080 for the root mean square error of approximation fit index based on previous trans-contextual models [9]. The analysis indicated that a student sample size of 286 is required to detect the effect size based on model fit. Based on typical attrition rates of 40% reported in the literature in multiple follow-up studies of physical activity [57, 58] we aim to recruit 476 student participants at baseline (*n* = 238 participants per intervention group).

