### Data analysis

Multilevel structural equation modelling using the Mplus, v. 8.0 software [59] will be used to test our hypotheses. All analyses will be performed using intention-to-treat analysis and supplemented by per-protocol analyses for all planned outcome variables [60]. Where data is missing for the psychological variables, we will impute missing values using linear interpolation if the data is confirmed missing completely at random. We expect to have data on our primary and secondary outcome measures, as well as mediating measures, at pre-trial and at the allotted follow-up occasions after the delivery of the intervention (post-trial, and at the one-, three-, and six-month follow up data collection occasions after the implementation period). We also expect to have self-report data on parenting from students and their parents or guardians at pre-trial. Student data will be nested within school and teacher/class, and therefore variance in outcome variables may be attributable to school-level and class-level variation as well as variation between students attributable to the intervention itself. Effects of the intervention on study outcomes can be interpreted at the student level after controlling for school- and class-level effects. Our longitudinal design enables also the examination of potential trajectories in the development of outcome variables. We will test the model at each of the follow-up time points with students’ out-of-school physical activity as the primary dependent variable, the intervention condition as a dummy-coded independent variable (1 = intervention group; 0 = control group), and the psychological variables (perceived autonomy support from teachers, autonomous motivation in PE and out-of-school physical activity, attitudes, subjective norms, perceived behavioural control, intentions), as simultaneous predictors. We will statistically control for each of model variables from the previous time point using the standardized residual scores.

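### The primary outcome is listed at five occasions, wrongly including pre-trial, and modelled separately at four follow-ups without saying which one decides the hypothesis

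*Protocol article*

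**What the plan says.** The hypothesis, in the Background of the Abstract, is directional and names no time: students receiving the programme "will exhibit greater participation in physical activities outside of school, relative to students receiving a control intervention".

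The section Primary outcome variable describes a post-intervention measure but places it as "participation in out-of-school physical activity at the pre-trial, post-trial, one-, three and 6 month follow-up data collection occasions", which is five occasions, the first before the intervention.

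The Data analysis section gives four occasions after the intervention ("post-trial, and at the one-, three-, and six-month follow up data collection occasions after the implementation period") and states: "We will test the model at each of the follow-up time points with students’ out-of-school physical activity as the primary dependent variable". It gives no significance level for these tests. It notes that the longitudinal design allows trajectories to be examined, but does not make a trajectory or any overall test the primary one.

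In the Sample size section, "student’s participation at each post-intervention follow-up occasion was regressed on the intervention condition" in the model behind the power analysis, and "statistical significance level (alpha) was set at 0.05". No occasion is singled out there either.

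The section Procedure and data collection methods has the wait-list teachers trained in the programme directly after the three-month collection, and so before the six-month one.

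**The concern.** A primary outcome should give one answer to the main hypothesis, or come with a rule for combining several. Here four tests carry equal primary status, so a significant result at any one could be presented as the trial's primary finding, and the occasion to stress could be chosen after the data are known.

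The four occasions also ask different questions. Post-trial comes directly after the implementation month. One and three months concern maintenance against controls not yet trained in the programme. Six months compares earlier-trained with later-trained teachers. An analyst who takes six months as decisive is testing a different contrast from one who takes post-trial or three months, and the text permits either.

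**Working it through.** **Plan's own figures.** The article states no error rate across occasions, so there is none to reproduce. Its recruitment target does reproduce, 286 / (1 - 0.40) = 476.7 against 476 stated, but that does not bear on this point.

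**Inputs from the article.** Four follow-up tests (Data analysis); three if six months is set aside because controls have by then been trained (Procedure and data collection methods). Level 0.05 (Sample size).

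**Assumptions.** The 0.05 is carried over to each outcome test. Tests are two-sided, since sidedness is not stated. One significant occasion is enough to claim success. The correlation between the test statistics is not given, so a range is shown.

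**Independent tests, no true effect.**
- Either direction, four occasions: 1 - 0.95^4 = 0.185.
- Either direction, three occasions: 1 - 0.95^3 = 0.143.
- Favouring the programme (0.025 per test), four occasions: 1 - 0.975^4 = 0.096.
- Favouring the programme, three occasions: 1 - 0.975^3 = 0.073.

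**Correlated tests.** Simulation of equally correlated z-tests, 1,000,000 draws per setting; the zero-correlation row is the exact value above.

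| Assumed correlation | 4 occasions, either direction | 4 occasions, favourable | 3 occasions, either direction | 3 occasions, favourable |
|---|---|---|---|---|
| 0 | 18.5% | 9.6% | 14.3% | 7.3% |
| 0.3 | 17.4% | 8.7% | 13.6% | 6.8% |
| 0.5 | 15.6% | 7.8% | 12.5% | 6.2% |
| 0.7 | 13.1% | 6.5% | 10.9% | 5.5% |
| 0.9 | 9.3% | 4.7% | 8.4% | 4.2% |

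The reference values for a single test are 5% in either direction and 2.5% favourable. Under any form of dependence, four tests cannot exceed 4 × 0.05 = 20% in either direction.

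**Pre-trial.** It adds no test. Objectives and Trial design both treat it as baseline, and Data analysis tests follow-ups only.

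**After the fix.** One named occasion returns the rate to 5%. If all four stay primary, Bonferroni gives 0.05 / 4 = 0.0125 each, and 1 - (1 - 0.0125)^4 = 4.9% if independent. Holm protects at the same overall level with at least as much power.

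**The case against.** Several objections have force.

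- **The protocol does not say that any one significant occasion means success.** True. The text leaves the rule open, so the rates above describe a reading it permits, not one it adopts.
- **The 0.05 belongs to a model-fit power calculation.** True. Applying it to the outcome tests is an inference.
- **Repeated measures on the same students are correlated.** True, and this lowers the figures, as the table shows. Adjusting each model for the previous time point, as the Data analysis section plans, would tend to weaken that correlation, so its size cannot be settled from the document.
- **The pre-trial listing is a drafting slip.** Probably so. It needs correcting but does not affect the error rate.
- **A mixed pattern does have a reading.** In part. The Discussion separates effectiveness from long-term effectiveness at one, three and six months, so an effect at post-trial that is gone by three months could be read as not maintained. That is an aim, not a ranking of the tests, and it does not say which result decides the hypothesis.
- **Multiplicity procedures usually sit in the analysis plan, which is not shown.** True, so the lack of one here is not the finding. The finding is the primary outcome definition and the test at each occasion, both of which this document fixes. A later plan naming one occasion would have to override them.

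**Conclusion.** The point holds. The primary outcome definition includes an occasion that cannot belong to it, and the primary test is repeated at four follow-ups with none named as decisive, one of them after the control arm has been trained.

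The size depends on the assumptions listed with the calculation. With no effect, the chance of some significant result is at most 18.5% for non-negatively correlated tests. The chance of one favouring the programme is at most about 9.6%, nearly four times the nominal 2.5%.

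A reader might infer that an ineffective programme has about a 19% chance of being declared beneficial. The documents do not support that: the 18.5% also counts results favouring control, while the hypothesis is directional. It would apply to favourable results only if each test were one-sided at 0.05, which the article does not state, and the nominal rate would then be 5%. Nor is an inflated error rate a fixed property of the plan, since it depends on a success rule that the plan leaves open. The matter should be corrected, but it does not undermine the design.

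**What to change.** In Primary outcome variable, name one primary occasion, chosen from those before the control teachers are trained. Three months is one defensible choice, as the last such occasion. Post-trial is another, as the direct test of effect after implementation. Accelerometry is collected at both, so it does not decide between them. In the same place, describe pre-trial as the baseline covariate and the remaining follow-ups as secondary, and carry the wording into Data analysis.

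If several occasions must stay primary, state either a fixed sequence, each tested at 0.05 only if the one before was significant, or Holm adjustment across them, and give the significance level and sidedness of the outcome tests.

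The change needs a few sentences and no new data. It does have a cost: occasions not named become supportive evidence. The change must also be dated, made before outcome data are seen, and matched to the trial registration.

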#### Secondary outcome variables

Physical activity behaviour. A subsample of participants (approx. 120) from representative school classes covering grades 7–9 will have their physical activity participation measured using accelerometry. The purpose of this secondary measure is to provide concurrent validity and comparison data to support the IPAQ used as the primary outcome measure.^2^ Participants will wear the accelerometers (Hookie AM 20) for seven consecutive days after each data collection occasions at pre-trial, post-trial, and at the three-, and six-month follow up data collection occasions. These accelerometers have been shown to be valid and reliable in as a measure of physical activity in previous research [2]. Participants will be also asked to complete a short diary of their daily in-school and out-of-school physical activities for the period during which they wear the accelerometer. Data will provide duration participants spent in sedentary, light, moderate, and vigorous intensity physical activity per day. Diary data will be used to identify duration of physical activity on in-school and out-of-school contexts. It will also provide a measure of total energy expenditure in each context. For the purposes of the current study, we will compute total time spent in light, moderate, or vigorous physical activity and total energy expenditure in out-of-school contexts as criterion measure to test the concurrent validity of the IPAQ measure in each participant. The accelerometry data will be included only for those participants who have provided valid accelerometer data for a minimum of 3 days.

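### The accelerometer criterion for the IPAQ includes light-intensity movement that the IPAQ does not ask about, so a low validity coefficient could not be attributed to poor self-report

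*Protocol article*

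**What the plan says.** Only the protocol article is at hand. Under Primary outcome variable, the modified short IPAQ records "participation in moderate and vigorous physical activity, walking, and sitting over the past 7 days". On scoring, the section says: "The physical activity score for moderate and vigorous physical activity and walking is calculated based on norms and expressed in MET-minutes per week". The next sentence describes the total as the "sum of the duration and frequency of vigorous, moderate and light physical activity scores". There is no light-activity item, so light stands where walking stood one sentence earlier.

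Under Secondary outcome variables, about 120 students wear an accelerometer. The aim is stated as: "The purpose of this secondary measure is to provide concurrent validity and comparison data to support the IPAQ used as the primary outcome measure". On output: "Data will provide duration participants spent in sedentary, light, moderate, and vigorous intensity physical activity per day". On context: "Diary data will be used to identify duration of physical activity on in-school and out-of-school contexts". The criterion consists of two out-of-school quantities: "we will compute total time spent in light, moderate, or vigorous physical activity and total energy expenditure in out-of-school contexts as criterion measure".

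**The concern.** The same word covers two different things. In the questionnaire total, light can only mean reported walking. In the accelerometer data it is an intensity class: movement above sedentary and below moderate, whether or not the student was walking. Some brisk walking may in turn fall in the accelerometer's moderate class. The two totals therefore have different content, although the shared label suggests that they match. The weighting differs too: the IPAQ components are in MET-minutes, while the time criterion adds minutes of all intensities equally.

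What is at stake is the interpretation of the validity check. The Discussion presents accelerometric verification of self-report as an advance on an earlier PE-delivered study. If the coefficient is low, the planned criterion alone cannot separate two explanations: students report their activity badly, or the accelerometer counts behaviour they were never asked about.

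**Working it through.** The protocol states no share of light activity, no spread and no target coefficient, so there is no figure to reproduce. The check sets the definitions side by side and then asks how far the mismatch could matter under assumed inputs.

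**1. Content and weighting**

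| | IPAQ total | Accelerometer time criterion | Accelerometer energy criterion |
|---|---|---|---|
| Vigorous | yes | yes | yes |
| Moderate | yes | yes | yes |
| Walking | yes (labelled light in the total) | yes, in whichever intensity class it falls | yes |
| Other light movement | no item | yes, unless the diary excludes it | yes, unless the diary excludes it |
| Weighting | MET-minutes | plain minutes | by energy |

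The row on other light movement is the mismatch. The weighting row adds a second difference for time only.

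**2. Share of the criterion (assumed inputs)**

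Let M be walking plus moderate plus vigorous minutes per day out of school, and L the light movement other than walking. Assume M = 60, with 2 MET for L and 4.5 MET for M.

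- Time share of L = L/(L + M). For L = 15, 30, 60, 120, 240 this is 20%, 33%, 50%, 67%, 80%.
- Energy share of L = 2L/(2L + 4.5M). For the same values this is 10%, 18%, 31%, 47%, 64%.

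So L is the larger part of time only if L > M, and of activity energy only if L > (4.5/2)M = 2.25M.

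**3. Ceiling on the time coefficient (assumed inputs)**

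Suppose students reported M without error. With k = SD(L)/SD(M) and rho = corr(M, L), the correlation of M with M + L is (1 + rho·k)/√(1 + k² + 2·rho·k).

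| rho | k = 0.5 | k = 1 | k = 2 |
|---|---|---|---|
| 0 | 0.89 | 0.71 | 0.45 |
| 0.3 | 0.92 | 0.81 | 0.64 |
| 0.6 | 0.96 | 0.89 | 0.81 |

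A negative rho lowers it further: at rho = −0.3 the values are 0.87, 0.59 and 0.21. With L = 0 the ceiling is 1.00 by construction.

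**4. An imperfect questionnaire (assumed inputs)**

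Here the criterion is split into moderate-to-vigorous time (MV, SD 20 min) and all accelerometer light time (LT, SD 30 to 50 min), with correlation 0.1 to 0.3 between them. The IPAQ is assumed to correlate 0.50 with MV.

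- *IPAQ related to light time only through MV.* r = 0.5(20 + rho·SD_LT)/SD(total). For example, with SD_LT = 30 and rho = 0.3: 0.5 × 29/√(400 + 900 + 360) = 14.5/40.7 = 0.36. With SD_LT = 50 and rho = 0.1: 0.5 × 25/√(400 + 2500 + 200) = 12.5/55.7 = 0.22. The range is 0.22 to 0.36. The implied IPAQ correlation with light time is only 0.5 × 0.1 = 0.05 to 0.5 × 0.3 = 0.15.
- *Walking item picks up some light time*, so that the IPAQ total correlates 0.3 with it. r = (0.5 × 20 + 0.3·SD_LT)/SD(total). For example, with SD_LT = 30 and rho = 0.1: 19/37.7 = 0.50. With SD_LT = 50 and rho = 0.3: 25/59.2 = 0.42. The range is 0.42 to 0.50.

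The loss against 0.50 thus runs from almost none to more than half, depending on an input that the protocol does not give.

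**The case against.** The strongest case against the point has five parts.

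- *Size.* A reader might infer that the check is dominated by movement the IPAQ never asks about. The document does not support that. Dominance follows only if light time is assumed to be large or highly variable, and the walking item may capture part of it. This objection stands.
- *The diary.* If only activities that students list in the diary count as out-of-school activity, incidental movement would largely drop out. The text allows that reading, and also the reading that the diary merely marks which wear time is out of school. The objection stands as a limit on size, and the ambiguity belongs to the same definition.
- *The energy criterion.* It weights by intensity, as MET-minutes do, so light minutes count for less there. This is correct and softens the concern for that comparison, but does not remove the difference in content.
- *Total against total is a defensible choice,* and moderate plus vigorous as sole principal criterion would drop walking, a scored part of the primary total. This also stands, so the planned comparisons should remain.
- *Consequence.* The check is secondary, no threshold or decision rule hangs on it, results by intensity band are available anyway, and extra correlations may be listed in a fuller plan. This limits the importance. It does not answer the point that the article itself fixes the criterion and uses one word in two senses.

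**Conclusion.** The point holds in a limited form. From the text alone, the criterion contains light-intensity movement outside the IPAQ items, and the label light conceals this. How much is not quantified and cannot be derived: the ranges above rest on assumed minutes, SDs, correlations and MET values, and run from minor to large. A low coefficient would therefore be ambiguous between content mismatch and poor self-report.

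A reader might go further and infer that the primary result is put in doubt. It is not: the criterion enters neither the definition of the primary outcome, nor the model in Data analysis, nor the Sample size calculation. This is an inexpensive improvement to the interpretation of a secondary check.

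**What to change.** 1. Under Primary outcome variable, call the third component of the IPAQ total walking.
2. Under Secondary outcome variables, keep the planned total-time and energy-expenditure comparisons, and pre-specify beside them a band-matched one: IPAQ moderate plus vigorous out-of-school minutes against accelerometer moderate plus vigorous out-of-school minutes. Interpret the total-time coefficient in its light. A good matched coefficient beside a poor total one would point to content; poor values on both would point to self-report.
3. In the same edit, say whether the diary limits the criterion to listed activities or only separates in-school from out-of-school wear time.

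The cost is wording and one more correlation, since both instruments already yield the components. The downside is that the matched comparison covers only part of the primary total, because it leaves out walking below moderate intensity. The match is also not perfect: brisk walking reported under the IPAQ walking item may be classed as moderate by the accelerometer.
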